## Abstract

**Background:**

Aphasia is a common and severely disabling complication in stroke patients. It usually brings about lower rates of functional recovery, longer rehabilitation length of stay (LOS), and significantly poorer LOS efficiency (LOS-Eff), resulting in higher rehabilitation costs compared to patients without aphasia. It also decreases the quality of life and increases the mortality of stroke patients. The evidence currently available suggests that the effect of acupuncture combined with language training for apoplectic aphasia is statistically better than speech and language therapy (SLT) alone, but there remains a lack of high-quality randomized controlled trials. Acupuncture combined with language training is relatively low-cost and especially suitable for community-based rehabilitation for aphasia patients after stroke, taking its medical and health facilities which are always deficient in manpower and material resources into account. The aim of the present study is to develop an effective standard therapeutic program for apoplectic aphasia in communities.

**Methods/Design:**

In a randomized controlled clinical trial with blinded assessment, 290 eligible patients with aphasia due to stroke will be randomly allocated into a control group or an experimental group. The course of this trial will comprise a 4-week intervention and a 12-week follow-up period. Five assessment points, including baseline, 2 and 4 weeks after treatment, 6 and 12 weeks after follow-up, are set to dynamically observe the changes of curative effects. Primary outcome measures are the differences in the score on both the China rehabilitation research center aphasia examination (CRRCAE) and Boston diagnostic aphasia examination - Chinese version (BDAE-C) after intervention and follow-up. The Modified Barthel Index (MBI), 36-Item Short Form Health Survey (SF-36), and results of blood oxygen level dependent-functional magnetic resonance imaging (BOLD-fMRI) examination are considered as the secondary outcome measures. Other outcomes will include rate of adverse events and economic effects.

**Discussion:**

If the outcome is positive, this project will offer a low-cost appropriate technology for community health centers (CHCs) in the rehabilitation of aphasia patients after stroke, and could be implemented on a large scale, both in China and worldwide.

**Trial registration:**

Chinese Clinical Trial Registry:
ChiCTR-TRC-13003703. Registration date: 18 October 2013.

## Background

Aphasia is a common complication in stroke patients, with lower rates of functional recovery
[1,2], longer rehabilitation length of stay (LOS), and significantly poorer LOS efficiency (LOS-Eff) compared to patients without aphasia
[3]. Furthermore, it proves that the occurrence of aphasia has an influence on the direct costs of rehabilitation
[4]. Language dysfunction in the post-acute or chronic phase after a stroke is the major restriction of vocational rehabilitation
[5] and reduces the probability of a return to work
[6]. Aphasia is associated with emotional burden
[7] and limits social participation owing to impaired communication ability
[8], as well as with a decrease in the quality of life
[9] and an increase in the mortality of stroke patients
[10]. Thus, there is an urgent need to search for one method which is both effective and low-cost for the rehabilitation of stroke patients, especially those discharged from hospital back into the community.

Although most patients with post-stroke aphasia present some degree of spontaneous recovery, this tends to plateau by one year after onset
[11]. Approximately 40 to 60% of patients move from the acute stage to the chronic stage if the condition persists 6 to 12 months after stroke
[12]. Speech and language therapy (SLT), the effectiveness of which is documented in a Cochrane systematic review on SLT for people with aphasia following stroke
[13], is the most common treatment
[14]. SLT in the acute stages of apoplectic aphasia is almost twice as effective as natural recovery alone
[15]. Unfortunately, current SLT has only limited effectiveness in improving aphasia, and other approaches adjunct to SLT might be used
[16].

As a typical traditional Chinese medicine, acupuncture has been applied for thousands of years
[17], and it has been widely used for aphasia rehabilitation in China. Many clinical studies about acupuncture therapy for aphasia have been conducted in the past few decades. It has been confirmed that acupuncture is an effective adjuvant therapy to SLT in the rehabilitation of aphasia
[14]. To obtain a more credible evaluation of the effect of acupuncture for post-stroke aphasia, Pang *et al*.
[18] performed a systematic review of the relevant randomized controlled trials, and the results support the conclusion that the effect of acupuncture combined with language training for apoplectic aphasia is statistically better than SLT alone. However, the included articles are assigned as low-quality by the authors, with a suggestion that more high-quality randomized controlled trials needed to be performed.

At present, professional rehabilitation of aphasia is offered mainly in high-grade hospitals, which are rich in interventional technologies but are relatively highcost. The heavy burden on families may be one of the major reasons for the early discharge of stroke survivors from hospitals
[19]. A study by Klebic *et al*.
[20] observed that only 21.2% of patients with aphasia continued language therapy after leaving hospital, which negatively affects functional recovery
[21]. The provision of stroke rehabilitation services in the community is supported by evidence
[19], and community-based rehabilitation for aphasia patients after stroke is especially important and urgently needed. Taking the medical and health facilities of community into account, the therapy we select for aphasia patients after stroke should be more effective, lowcost, convenient, and uncomplicated. Scalp acupuncture treatment, which meets the above requirements, will be a suitable selection.

The goal of the present study, combined with a randomized, parallel-controlled design, is to develop an efficacious and economical therapeutic program for apoplectic aphasia in communities. Finally, it will be implemented on a large scale if it is found to be an appropriate technology.

## Methods/Design

### Study design

The current study uses a multicentre, cluster randomized, parallel-controlled superiority design with blinded assessment (a flow diagram of the study design is presented in Figure 
1). The course of this trial will comprise a 4-week intervention and a 12-week follow-up period. The control group will receive SLT and initial therapies, while, the experimental group will receive additional scalp acupuncture. There is a total of five time points, including baseline, 2 weeks after treatment, 4 weeks after treatment, 6 weeks after follow-up, and 12 weeks after follow-up. Fujian University of Traditional Chinese Medicine (FJTCM), as an undertaker of this project, is responsible for completing the training of the rehabilitation therapists in a unified standard way before the study, and supervising their operations regularly during the study at all clinical sites. The Center of Evidence-based Medicine in FJTCM, which plays a role in randomization and will be blinded to the intervention, is an independent department employed to monitor and analyze data. The present project, funded by the State Administration of Traditional Chinese Medicine, has received approval from the local ethics committees of every center (Fujian: 2013KY-006-01, approval received in July 2013; Henan: 2014HL010, approval received in March 2014; Shandong: 2013KY-006-01, approval received in March 2014) participated in the study. Written informed consent is required prior to participation from each participant or their guardian, and they will be informed of the nature of this trial including its purpose, procedures involved, expected duration, potential risks and discomfort, as well as the possible benefits they will receive from it. There is no time limit for them to ask related questions and respond to the invitation to participate. Participants will be also informed that they are free to withdraw from the study at any stage for any reason and their personal information will be undisclosed and kept securely at FJTCM.

**Figure 1 F1:**
[figure not shown]
Flow diagram of study design.

### Participants and recruitment

The protocol will be carried out at community health centers (CHCs) run by three sub-centers, including the Affiliated Rehabilitation Hospital of Fujian University of Traditional Chinese Medicine (Fujian province, China), the Second Affiliated Hospital of Shandong University of Traditional Chinese Medicine (Shandong province, China), and the First Affiliated Hospital of Henan College of Traditional Chinese Medicine (Henan province, China). Many CHCs in different areas of the three provinces will be included in this protocol, providing a large number of patients.

### Inclusion criteria

The eligible participants should meet all the following criteria: (1) have been diagnosed with stroke according to the criteria regulated by the Fourth National Cerebral Vascular Disease Conference
[22], and confirmed as first stroke by a computed tomography (CT) or magnetic resonance imaging (MRI)examination; (2) be no more than two years post-stroke; (3) suffer from Broca’s aphasia after stroke, determined by the neurologist or rehabilitation physician and speech and language therapist, ascertained with Chinese Rehabilitation Research Center Standard Aphasia Examination (CRRCAE); (4) be between 18 and 80 years of age; (5) have provided written informed consent.

### Exclusion criteria

Patients having anyone of the following will be excluded: (1) aphasia due to another encephalopathy, such as traumatic brain injury, brain tumor, neurodegenerative diseases, brain parasitic diseases and so on; (2) aphasia due to dementia or dysarthria; (3) stroke with serious uncontrolled complications, such as severe pulmonary infection, shoulder-hand syndrome or deep vein thrombosis; (4) having severe uncorrected to normal visual or auditory impairment; (5) having serious heart, kidney, liver, or nervous system disease; (6) having a history of epilepsy; (7) having received an alternate intensive intervention which may affect the evaluation results during the last 4 weeks;

### Sample size

Referring to a trial
[23] with the same protocol as the present study, the effective rate of Broca’s aphasia after stroke was 64.71% in the control group (π_1_) and 85% in the experimental group (π_2_). Preliminary epidemiological findings show that there will not be less than 16 qualified participants recruited from each CHC. Prior data indicates that the intra-CHC correlation coefficient (ρ) is likely to be 0.030. Each group will consist of 132 individuals according to the formula:

(1)$$n=\frac{{\left(\mu_{\alpha }+\mu_{\beta }\right)}^{2}\;\left[\pi_{1}\;\left(1-\pi_{1}\right)+\pi_{2}\;\left(1-\pi_{2}\right)\right]\left[1+\left(m-1\right)\;\rho \right]}{{\left(\pi_{1}-\pi_{2}\right)}^{2}}$$

with a type I error of 5% (α = 0.05) and 90% power (β = 0.10). There will be 290 subjects included in total, allowing for a dropout rate of 10%.

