### Primary outcomes

The primary outcome measures in this study are the differences in the scores on both the CRRCAE and the aphasia grading standard of severity in BDAE-C after intervention and follow-up between the two groups and within groups.

The CRRCAE
[27,28] was made by Chinese Rehabilitation Research Center with the help of Japanese experts according to Chinese language and cultural habits by referring to the Japanese Standard language Test of Aphasia (SLTA). It consists of two parts. One part includes twelve questions about demography date and is used to test the patients’ general condition of speech. The other part contains nine subtests (auditory comprehension, repetition, speaking, reading aloud, reading comprehension, copying, description, dictation, and calculation). There are 30 quizzes in total, with three or four quizzes in each subtest. This scale has been used widely in hospitals and rehabilitation centers in China with a good reliability and validity. The interclass correlation coefficients (ICC) of test-retest reliability exceeded 0.9, the Cronbach’s α of internal consistency was 0.941, and the relationship with the Western Aphasia Battery (WAB) was 0.948 (on aphasia quotients). Furthermore, we can diagnose whether a person has aphasia and, if so, the degree of severity from the result of CRRCAE which can guide the strategies of therapy and can also measure the outcomes of treatment.

BDAE
[29] is a widely used aphasia examination in the world. As the BDAE original edition is not suitable for Chinese conditions, it was revised to BDAE-C
[30,31] based on the Chinese culture and language background, and is now established as the standard for Chinese patients. There are six grades in the aphasia grading standard of severity in BDAE-C from the worst to the best in the order of 0 to 5.

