### Statistical methods

Statistical analysis in this study will be performed by a statistician who is not involved in this trial and works in the Center of Evidence-based Medicine in FJTCM. Analysis of all data will be conducted with SAS software (version 8.2, SAS Institute, Cary, North Carolina, United States), and two-sided *P* < 0.05 was considered statistically significant.

Descriptive statistics will be expressed in different forms according to the types of the data in each group. That is to say, continuous variables will use mean and standard deviation for normal distribution, with median and interquartile range for non-normal distribution, and categorical variables will use proportions with their standard error. Comparison of baseline characteristics, the primary or secondary outcomes between groups will use the *t*-test or Mann-Whitney test for continuous variables and Pearson chi-squared or Fisher’s exact test for categorical variables. Changes in effect sizes of primary or secondary outcomes from baseline to each time point for two groups will be expressed using the paired *t*-test or Wilcoxon signed-rank test.

The primary outcomes will be analyzed using full analysis set (FAS) and per protocol set (PPS), with the secondary outcomes using FAS. Analysis of the primary and secondary outcomes should be on the basis of the intention-to-treat (ITT) population. The safety set (SS) will be used to assess adverse events.

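### The 90% power is for a binary effective rate that the protocol neither defines nor lists, so it does not apply to either primary outcome

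*Protocol article*

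**What the plan says.** The Sample size section of the protocol article cites a trial said to have followed an identical protocol. That trial's effective rate for Broca's "aphasia after stroke was 64.71% in the control group", against "85% in the experimental group". The section puts these rates into a two-proportion formula with a design effect. For the clustering it states that "there will not be less than 16 qualified participants recruited from each CHC" and that the intra-CHC correlation "is likely to be 0.030". With a type I error of 5% and 90% power it reaches 132 per group, raised to 290 in total for 10% dropout.

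The Primary outcomes section reads: "The primary outcome measures in this study are the differences in the scores on both the CRRCAE and the aphasia grading standard of severity". The severity standard meant is the BDAE-C one, with six ordered grades, 0 to 5, and both scales are compared at the end of treatment and at follow-up.

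The effective rate appears only under Sample size. It is absent from the abstract's list of outcomes, from the primary and secondary outcome sections, from the safety and economic sections and from Table 1. The Statistical methods section compares outcomes by t-test or Mann-Whitney test if continuous and by chi-squared or Fisher's exact test if categorical. It names no responder analysis.

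**The concern.** The size and the power of a trial should refer to its primary question. Here they refer to a two-category outcome with no stated scale, cut-off or time point, while the primary outcomes are a score and an ordinal grade. The formula contains nothing about the mean, spread or distribution of either scale, so its 90% cannot be carried over to them.

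Two things are at stake. A null result on CRRCAE or BDAE-C could not be read against the stated power. And while the effective patient stays undefined, this document does not prevent a responder cut-off from being chosen after the data are seen.

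**Working it through.** **Inputs from the Sample size section.** π₁ = 0.6471, π₂ = 0.85, m = 16, ρ = 0.030, α = 0.05, power 0.90. The test is two-sided, as stated under Statistical methods.

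**1. The plan's own figure.**
- Design effect: 1 + (16 − 1) × 0.030 = 1.45.
- Variance term: 0.6471 × 0.3529 + 0.85 × 0.15 = 0.2284 + 0.1275 = 0.3559.
- Before clustering: (1.960 + 1.2816)² × 0.3559 / 0.2029² = 90.83.
- With clustering: 90.83 × 1.45 = 131.7, so 132.

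The stated 132 reproduces. Effective n is 132 / 1.45 = 91.0 per group, and at that size power for 64.71% against 85% is 90.1% with the formula's unpooled variance. The 90% is therefore the power of the binary comparison.

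**2. What the same size gives for a continuous score.** The document has no SD, target difference or ICC for CRRCAE, so this step rests on assumptions: 132 evaluable per group, 16 per centre, and an analysis that allows for clustering. The standardised difference detectable with 90% power is

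d = (1.960 + 1.2816) × √(2 × [1 + 15 × ICC] / 132).

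| Assumed ICC | Design effect | Detectable d |
|---|---|---|
| 0.01 | 1.15 | 0.43 |
| 0.03 | 1.45 | 0.48 |
| 0.05 | 1.75 | 0.53 |
| 0.10 | 2.50 | 0.63 |

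These values use normal quantiles. With few centres, t quantiles are more apt. The 290 enrolled at 16 per centre make about 18 centres, hence 18 − 2 = 16 df. At ICC 0.03, d = (2.120 + 1.337) × √(2/91.0) = 0.51. Counting the 264 evaluable instead (16 to 17 centres, 14 to 15 df) changes this only to between 0.51 and 0.52.

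**3. Power over a range of assumed true differences** (ICC 0.03, normal quantiles), from Φ(d / √(2/91.0) − 1.960):

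| Assumed d | Power |
|---|---|
| 0.2 | 27% |
| 0.3 | 53% |
| 0.4 | 77% |
| 0.5 | 92% |
| 0.6 | 98% |

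Nothing in the document picks a row.

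**4. BDAE-C severity grade.** No detectable difference can be computed. An ordinal calculation needs the expected distribution over the six grades, which is not given.

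**The case against.** The strongest case on the other side has four parts.

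- **The power may be ample.** A reader might infer from the mismatch that the trial is too small. The documents do not support that. Suppose that effective means passing a cut-off on a roughly normal score with equal SDs. The plan's rates then imply z(0.85) − z(0.6471) = 1.036 − 0.377 = 0.66 SD. On the basis of the working, power at 0.66 SD is about 99% at ICC 0.03, 98% at 0.05 and 92% at 0.10. This stands as a warning against reading underpowering into the point. It does not rescue the stated 90%, because the document ties the effective rate to neither scale and gives no cut-off.
- **The trial may yet analyse an effective rate.** Chi-squared and Fisher tests are planned for categorical variables, and an analysis plan not at hand could define a responder. So it would be too strong to say that the trial will never make this comparison. What the document supports is that it neither defines the comparison nor lists it. A responder definition elsewhere would still leave score and grade differences as the declared primary outcomes.
- **The article links the 90% openly to the two rates.** That is true; it does not claim in words 90% power for CRRCAE or BDAE-C. But it is the only power given, and it stands as the justification for the trial's size.
- **No estimate is biased and the type I error is unaffected.** This also stands, and a null result can still be read from its confidence interval. The fault lies in the justification of the size, not in the validity of the result.

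**Conclusion.** The point holds in this form: 132 per group and 90% power describe an undefined, unlisted binary outcome, and the 90% applies to neither primary outcome. This follows from the text alone and needs no assumption.

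Its size can be shown only conditionally. For CRRCAE, 90% power corresponds to about 0.48 SD at ICC 0.03 (about 0.51 SD with 16 df), and to between 0.43 and 0.63 SD over ICCs of 0.01 to 0.10. Two conditions need stating. The 0.030 is given without naming an outcome, so it need not hold for CRRCAE. And the figures presume a cluster-adjusted analysis, whereas the Statistical methods section names ordinary two-group tests. For the BDAE-C grade no figure is available. Whether the trial is adequately powered for its primary outcomes is left open by the document, in both directions.

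**What to change.** Keep the sample size and revise the Sample size section as follows.

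1. State that the 90% power refers to the effective rate of the cited trial only.
2. Restate the detectable difference for both primary outcomes under a cluster-adjusted analysis: CRRCAE from the sponsor's own SD and ICC, and BDAE-C grade from the expected grade distribution and its own ICC. If no better ICC for CRRCAE is at hand, give 0.48 SD at 0.03 (0.51 SD with about 16 df) together with the range 0.43 to 0.63 SD, label these as assumptions, and convert them to points with the SD.
3. If an effective rate is to be reported, define its scale, cut-off and time point before unblinding, and label it secondary or supportive.

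Steps 1 and 2 cost a rewritten paragraph and the retrieval of an SD, a grade distribution and two ICCs; no patients are added. Step 3 costs a short definition. Making the effective rate primary instead would not be cheap. The Trial status section says that the trial began in November 2013, and the Discussion says that it is not double-blind, so replacing the primary outcome now would be a substantive amendment with its own risk of bias.

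### The total of 290 covers about 9% dropout, not 10%, and the stated 90% power takes no account of the small number of randomised CHCs

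*Protocol article*

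**What the plan says.** All of the planning figures are in the Sample size section of the protocol article.

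- The assumed effective rates are 64.71% (control) and 85% (experimental), with a 5% type I error and 90% power.
- On cluster size, the section expects that "there will not be less than 16 qualified participants recruited from each CHC".
- On clustering, it says that "the intra-CHC correlation coefficient (ρ) is likely to be 0.030".
- On the result: "Each group will consist of 132 individuals according to the formula". The formula shown is the normal-quantile formula for two proportions multiplied by the design effect 1 + (m − 1)ρ.
- On the total: "There will be 290 subjects included in total, allowing for a dropout rate of 10" per cent. The step from 132 per group to 290 is not shown.

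The Abstract repeats the total of 290. The Study design and Randomization and blinding sections make the CHC the unit of allocation. The number of CHCs is not given; Participants and recruitment says only that there will be many. The Statistical methods section sets the test level: "two-sided *P* < 0.05 was considered statistically significant".

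**The concern.** Two statements about the sample size do not follow from the section's own inputs.

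First, if 132 per group is what the formula requires, a total that allows for 10% dropout must still leave 264 after one tenth has been lost. A total of 290 does not.

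Second, normal quantiles treat the standard error as known. In a cluster-randomised comparison it is estimated from the variation between clusters, so the degrees of freedom depend on the number of CHCs. With few CHCs the critical value exceeds 1.96 and power is lower than the formula says. The design effect corrects the variance but not this.

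At stake is whether the total and the 90% power can be quoted as they stand.

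**Working it through.** **Inputs.** p1 = 0.6471, p2 = 0.85, α = 0.05, power 90%, m = 16, ρ = 0.030, dropout 10%, total 290 (all from Sample size). Two-sided testing is from Statistical methods; it is also the only choice that reproduces 132, since one-sided gives 107.3.

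**1. The plan's own figure.**
- Variance term: 0.6471 × 0.3529 + 0.85 × 0.15 = 0.35586.
- Squared difference: 0.2029² = 0.041168.
- Without clustering: (1.960 + 1.2816)² × 0.35586 / 0.041168 = 90.83.
- Design effect: 1 + 15 × 0.03 = 1.45.
- n = 90.83 × 1.45 = 131.7, so 132 per group and 264 in total. The figure reproduces.

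**2. The dropout allowance.**
- 290 × 0.9 = 261, or 130.5 per group: three short of 264 in total.
- 1 − 264/290 = 8.97%, the largest dropout that 290 can absorb.
- 264/0.9 = 293.3, so 294 for a 10% allowance.
- 264 × 1.1 = 290.4, which fits the printed 290.

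**3. Effect of the slip by the protocol's formula.** Power = Φ(0.2029/SE − 1.960), with SE = √(0.35586 × design effect / n).
- n = 132, design effect 1.45: 90.1%.
- n = 130.5, design effect 1.45: 89.7%.
- n = 130.5, with dropout spread evenly so that m falls to 14.4 (assumption) and the design effect to 1 + 13.4 × 0.03 = 1.402: 90.7%. The requirement is then 90.83 × 1.402 = 127.3, so 128 per group, which 130.5 meets.

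**4. Number of CHCs (derived, not stated).** 290/16 = 18.1. With at least 16 patients in each, 290 patients fill at most about 18 CHCs, or 9 per arm.

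**5. Power with a t reference.** For k CHCs per arm, df = 2k − 2 and λ = 0.2029/SE. Power is the probability that a noncentral t with parameter λ exceeds the two-sided 5% critical value.

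| CHCs per arm | df | Critical t | n per group | Design effect | λ | Power |
|---|---|---|---|---|---|---|
| 9 | 16 | 2.120 | 130.5 | 1.45 | 3.227 | 85.7% |
| 9 | 16 | 2.120 | 130.5 | 1.402 | 3.282 | 86.8% |
| 9 | 16 | 2.120 | 145 (no dropout) | 1.45 | 3.401 | 89.1% |
| 9 | 16 | 2.120 | 132.3 (294 less 10%) | 1.45 | 3.249 | 86.2% |
| 8 | 14 | 2.145 | 130.5 | 1.45 | 3.227 | 85.1% |

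With 8 per arm, the mean evaluable cluster size is 130.5/8 = 16.3, the design effect is 1.459 and power is 84.8%, so about 85% either way.

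**The case against.** The strongest reply is that the dropout slip has no practical consequence. It amounts to 1.5 patients per group; 290 differs from 294 by 1.4%; and if dropout thins each CHC evenly, the protocol's formula still gives more than 90%. That stands for the slip taken alone. The even-thinning rescue does, however, require 16 to be the enrolled cluster size, and the section gives 16 as a minimum. Were CHCs to average 20 evaluable patients (an assumption), the design effect would be 1.57, the requirement 90.83 × 1.57 = 142.6, so 143 per group, and 130.5 would give 87.3% by the normal formula.

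A second reply is that the number of CHCs is not in the document, that the formula as printed was applied correctly, and that the t reference is a refinement and not a correction of arithmetic. This also stands in part: the power of 86 to 87% is conditional on about 9 CHCs per arm. But the count is bounded by the section's own minimum of 16. More CHCs would mean fewer than 16 patients in each at a total of 290, and the cap would lapse only if that minimum were given up.

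A reader might go further and infer three things that the document does not support:

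- That the authors multiplied 264 by 1.1. This fits 290.4, but no step is shown, and 293.3 rounded to a convenient figure would also give 290. On either route, 290 does not cover 10%.
- That 290 or 132 is wrong because it is not a multiple of 16. Sixteen is a minimum and CHCs may differ in size.
- That the dropout slip leaves the trial underpowered. The calculations in step 3 do not show that.

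**Conclusion.** The sentence on the total contradicts the requirement stated just before it: 290 covers about 9.0% dropout, and 10% needs 294. Its own effect is minor, from 90.1% to 89.7% by the protocol's formula, and nil if clusters shrink to 14.4.

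The larger but conditional point is the reference distribution. On the protocol's own rates and ICC, with 9 CHCs per arm, power after 10% dropout is about 86 to 87%; with 8 per arm it is about 85%. With 9 per arm and no dropout at all it is 89%, still below 90%, and raising the total to 294 does not close the gap.

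The conditional figures assume CHCs of similar size, an ICC of 0.03, an analysis that respects clustering (as the design effect presupposes), and at most about 18 CHCs. They concern the effective rate used for planning; the primary outcomes are CRRCAE and BDAE-C scores, for which the section gives no power. This is a correction to stated figures and does not make the trial invalid.

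**What to change.** Restate the sentence in the Sample size section in one of two ways: keep 290 and say that it allows for about 9% dropout, or give 294 for 10%. Show the inflation step.

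State the number of CHCs per arm, and replace the 90% with the power for that number from a t reference: about 86 to 87% after 10% dropout if there are 9 per arm and the ICC is 0.03. Say whether 16 counts enrolled or evaluable patients, since the design effect after dropout depends on it.

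The cost is a few sentences. No extra patients are needed if 290 is kept with the lower allowance; choosing 294 adds four. The downside is a slightly less favourable stated power.
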